#### Phonocardiogram data and fNIRS data

3.4.1

Heart sounds to be used as stimuli and for monitoring purposes will be converted into Mel spectrograms and input into neural networks trained with sound (OpenL3, YAMNet, and VGGish), and transfer learning will be performed.

Cognitive assessment will be performed by analyzing fNIRS signals to assess activation in specific brain regions (right, center, and left). The details are provided below. During mental stress, classification analyses will be performed between the results between the control and treatment groups and between the results of the same group before and after treatment. Then, using explainable artificial intelligence (XAI) techniques, the temporal and frequency-domain characteristics associated with these changes will be evaluated.

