#### Study design

3.1.2

An intervention and control group will be formed with 20 and 10 participants, respectively. The intervention and control groups will be exposed to the same mental stress.

*Control group:* 10 young healthy earthquake survivors will not receive any auditory stimulation.

Intervention group: 10 young healthy earthquake survivors will be subjected to closed-loop, real-time heart sound (PCG) stimulation to create biofeedback.Intervention group: 10 young healthy earthquake survivors will be given an auditory stimulus of their heart sound and a metronome synchronized with their mean heart rate (MHR) recorded during a calm state.

Participants will be taken individually to the experimental room and seated comfortably in a quiet and spacious environment. Before the first session, a scientific introduction, the purpose of the study, an explanation of how it will be conducted, an explanation of the mental stress to be induced, and basic information about the measurements to be taken will be provided at the information meeting (using an introduction video). The participant should feel as comfortable as possible, and no additional sources of stress should be created. Participants will be instructed to breathe normally and avoid moving their legs.

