**Figure 3 fig3:**

After 4 weeks, the procedure to be applied to all groups.

In this context, earthquake victims’ emotional and psychological states will be monitored using biomedical signals, and responses will be derived from these signals. Respiratory rhythm, electrocardiography (ECG), phonocardiography (PCG) (Özcan, 2024), electrodermal activity (EDA), and functional near-infrared spectroscopy (fNIRS) measurements will be performed during the information session, at the beginning of the sessions, throughout the 10 intervention sessions, and 4 weeks after the intervention (Arsalan et al., 2023). The application after about 4 weeks is to see whether the intervention is permanent.

Stress, anxiety, and depression will be assessed using psycho-emotional stressors at the beginning and end of the intervention using the Turkish version of the Depression Anxiety Stress Scale–21 (DASÖ-21) (Yıldırım et al., 2018).

Live heart sounds or average heartbeat sounds will be used as stimuli to provide biofeedback. A metronome will also be used for the auditory stimuli, including the heart rate from the ECG and the measured phonocardiogram. The audio stimulus will be presented at an intensity of 60–65 ± 10 dB before and during mental stress.

Different mental stress tasks will be induced in all sessions and 4 weeks after the sessions. A mental arithmetic task is a mechanism that increases the mental workload by performing a series of arithmetic operations of varying degrees of difficulty. One of the effective platforms used in the literature is Millisecond (Millisecond Software, Seattle, WA, USA), and the Trier Mental Challenge Test (TMCT) available through the Inquisit application will be used in the study. Millisecond Software is a leading software provider for psychological testing. The Inquisit platform has been used in applied fields, such as clinical trials, and several peer-reviewed studies. The TMCT is a timed arithmetic test designed by Kirschbaum to induce psychological stress in participants (Kirschbaum, 1991). During the session and throughout the 10 sessions, the mental operations should be randomized in order to create stress without allowing learning to occur.

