#### ECG, EDR, and fNIRS data

3.4.2

The data obtained using deep learning techniques will be classified. Classification studies will be performed with deep learning to emphasize to characterize differences between the control and treatment groups, as well as differences before and after treatment within groups and to show that the difference is significant. The data will be converted into spectrogram images and processed as time-series data. A suitable pretrained network (AlexNet, SqueezeNet, GoogLeNet, etc.) will be used with transfer learning, and classification will be performed. Technical information is provided in our published articles (Özcan and Alkan, 2021, 2023a, 2023b).

On the other hand, correlation analysis will be performed using deep learning method (Alessandrini et al., 2023). Then, the features used in the classification will be evaluated using explainable artificial intelligence techniques.

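### During the session stress task, control versus treatment is also silence versus sound, so classification accuracy does not by itself show benefit

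*Protocol article*

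**What the plan says.** Section 3.1.2 of the protocol article defines three arms that face the same stressor:

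- Control: "10 young healthy earthquake survivors will not receive any auditory stimulation".
- First intervention arm: "10 young healthy earthquake survivors will be subjected to closed-loop, real-time heart sound (PCG) stimulation to create biofeedback".
- Second intervention arm: "10 young healthy earthquake survivors will be given an auditory stimulus of their heart sound and a metronome synchronized with their mean heart rate", taken from a calm recording.

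Later in the same section, after the Figure 3 caption, the timing is fixed: "The audio stimulus will be presented at an intensity of 60–65 ± 10 dB before and during mental stress".

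Section 3.4.1 then sets the comparison: "During mental stress, classification analyses will be performed between the results between the control and treatment groups". The same sentence adds a comparison within each group, before against after treatment.

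Two places say what classification is for. Section 3.4 assigns it the evaluation of the biofeedback's benefits. Section 3.4.2, on ECG, EDR and fNIRS, wants it to characterise differences between and within groups and "to show that the difference is significant".

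Section 3.5.2 favours audio-pretrained networks for fNIRS recorded while sound is delivered. Section 3.5.3 judges the classifiers by accuracy, sensitivity, specificity, precision and F1. Section 5 concedes that there is no acoustically matched sham.

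**The concern.** In the session stress recordings, everyone labelled as treated is hearing something and everyone labelled as control is not. A network given fNIRS, electrodermal or cardiac signals can succeed by learning the immediate response to sound, whether or not stress regulation has changed.

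The listed metrics have no direction. Better regulation, added distraction and plain hearing would all raise accuracy. A high figure could therefore be reported as evidence that the biofeedback works when the same figure could arise with no therapeutic effect. Splitting training and test data by participant would not help, because the sound is there for every treated participant.

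**Working it through.** **Step 1: the text side by side.**

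| Element | Control | Real-time heart sound | Heart sound and metronome at mean heart rate | Source |
|---|---|---|---|---|
| Stressor | same | same | same | 3.1.2 |
| Sound during session stress | none | yes | yes | 3.1.2 |
| Class in the between-group classifier | control | treatment | treatment | 3.4.1 |

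The last two rows carry the same information: in these recordings, class equals sound off or on. Nothing in the article limits the between-group classification to sound-free or sound-matched recordings.

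**Step 2: the plan's own figure.** The only size given for the classification data is 1980 segments per measurement (section 3.5.2). 330 min × 60 s/min ÷ 10 s = 1980. It reproduces and is not in dispute. It has no bearing on the confounding, since more windows of the same kind carry the same label.

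**Step 3: illustration under zero benefit.** The article gives no size for the response to sound, so d below is an assumption. Let one window-level feature be normal with SD 1, and shifted by d only while sound is heard. With the cut-off midway between the two means, sensitivity and specificity both equal Φ(d/2), so balanced accuracy is Φ(d/2).

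| Assumed d (SD) | Φ(d/2): sound in treated arms only | Sound absent or matched |
|---|---|---|
| 0.5 | Φ(0.25) = 0.599 | 0.50 |
| 1 | Φ(0.5) = 0.691 | 0.50 |
| 2 | Φ(1) = 0.841 | 0.50 |
| 3 | Φ(1.5) = 0.933 | 0.50 |

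**Step 4: check by simulation.** The simulation used 10 control and 20 treated participants, training and test sets split by participant, and 200 repetitions. For d = 1, 2 and 3 it gave balanced accuracy of 0.693, 0.844 and 0.933 with sound in the treated arms, and 0.501, 0.501 and 0.500 without. The autonomic outcome was generated with no arm effect, and its mean arm difference was −0.006, 0.028 and −0.015. The simulation confirms the formula and shows that a participant-level split does not remove the effect. It says nothing about the true d in this trial.

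**The case against.** The strongest reply is that sound during stress is the intervention itself. The Background describes a participant who hears the heart rhythm rise and calms down, and section 5 asks whether people manage acute stress better with it. Treated against silent control during stress is the direct contrast for that question, while silent recordings would answer a different one, namely carry-over. This stands: the contrast should be kept. What fails is reading undirected separability as benefit.

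A second reply is that section 5 already declares the missing sham and offers the three arms as a partial separation of effects. That is largely the same confound. But section 5 speaks of mechanism, does not mention the classifiers, and leaves the aims in 3.4 and 3.4.2 unqualified. The sentence in 3.4.1 also names control against treatment, not the two sound arms against each other.

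Explainability maps do not answer the point. They show which regions of the input matter, but cannot tell a sensory response from a therapeutic one when the two coincide.

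Some stronger readings are tempting but not supported:

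- That every classification window is confounded. A stress task is also given 4 weeks after the sessions, and whether sound plays there cannot be seen because the figures are not shown. Section 3.4.2 does not itself name the stress window. The within-group classification is not labelled by arm; if before and after mean the first and last sessions, treated participants hear sound at both, but the article does not define those time points for the classifiers.
- That the phonocardiogram sensor picks up the stimulus. This is possible but is an assumption, and the point does not need it.
- That the analysis would show there is no benefit, or that the primary analysis is compromised. Neither follows. Section 3.5.1 analyses RMSSD, HF and LF by a mixed model or ANCOVA, which estimates a difference with a direction, in a study described as preliminary.

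**Conclusion.** The point holds for the session mental-stress recordings: the control-versus-treatment label coincides with sound off or on, so accuracy there does not by itself demonstrate benefit or a meaningful significant difference, as sections 3.4 and 3.4.2 intend. This follows from the text of 3.1.2 and 3.4.1 without the figures.

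Its numerical size is unknown. The 60% to 93% range is an illustration for assumed shifts of 0.5 to 3 SD in a single feature with no therapeutic effect. The defect lies in the inference drawn from a secondary analysis. It is worth correcting because the article states that inference and the correction is cheap.

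**What to change.** In sections 3.4.1 and 3.4.2:

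1. Keep the during-stress control-versus-treatment classification, described as exploratory discrimination. Remove its use to show significance and, in section 3.4, as evidence of benefit. Cross-refer to the missing-sham limitation in section 5.
2. Add a during-stress classification of the real-time heart-sound arm against the metronome/mean-heart-rate arm, where both hear sound.
3. Rest any benefit claim on directional measures such as the section 3.5.1 outcomes.
4. If the procedures before the first session and at 4 weeks are confirmed to be sound-free in all arms, also run the between-group classification there, and compare separation at 4 weeks with separation before the sessions as a test of carry-over. This depends on figures not shown, so it is conditional.

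Items 1 and 3 cost only rewording. Item 2 uses recordings already planned, but with fewer participants and windows: at 10 per arm, 20 participants instead of 30. Headline accuracy will probably be lower.

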#### ECG, EDR, and fNIRS data

3.4.2

The data obtained using deep learning techniques will be classified. Classification studies will be performed with deep learning to emphasize to characterize differences between the control and treatment groups, as well as differences before and after treatment within groups and to show that the difference is significant. The data will be converted into spectrogram images and processed as time-series data. A suitable pretrained network (AlexNet, SqueezeNet, GoogLeNet, etc.) will be used with transfer learning, and classification will be performed. Technical information is provided in our published articles (Özcan and Alkan, 2021, 2023a, 2023b).

On the other hand, correlation analysis will be performed using deep learning method (Alessandrini et al., 2023). Then, the features used in the classification will be evaluated using explainable artificial intelligence techniques.

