**Figure 1 fig1:**

Procedure to be applied to all groups before the first session.

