### Data analysis

3.4

Mood assessment will be conducted as described below using methods to analyze pre- and post-treatment questionnaires and by examining changes in parameters derived from biological signals (RMSSD, LF, HF, LF/HF, SDNN, SCL, SCR, and respiratory rate). Statistical methods will be used to analyze and evaluate the data obtained from the collected stress and anxiety questionnaires. In addition to respiratory rate, ECG, PCG, EDR signals, heart rate, heart rate variability (HRV), low-frequency band (LF) and high-frequency band (HF) indicators from the HRV signal, the LF/HF ratio, SDNN, RMSSD, and pNN50 parameters will be processed. Functional NIRS will be used to monitor brain functions in real time. These analyses will be based on changes in oxygenated and deoxygenated hemoglobin concentrations in the cerebral cortex. In particular, the prefrontal cortex region and limbic lobe (Balters et al., 2021; Dattola et al., 2023) will be monitored. Changes in the obtained signals and parameters change before, during, and after the intervention will be analyzed. Statistical techniques, deep learning, and explainable artificial intelligence (XAI) techniques will be used for this purpose. To evaluate the benefits and differences of the biofeedback study, classification analyses will be performed on the data.

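### The arm classification and the before/after classification are run separately and never combined, so an entry difference between non-randomised arms can be read as a treatment effect

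*Protocol article*

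**What the plan says.** Section 3.4.2 uses deep-learning classification "to characterize differences between the control and treatment groups". The same sentence goes on to a second task and an inference, so that in full it covers "differences between the control and treatment groups, as well as differences before and after treatment within groups and to show that the difference is significant". Section 3.4.1 plans the same pair for fNIRS under mental stress, "between the results between the control and treatment groups and between the results of the same group before and after treatment". Section 3.4 states the purpose: "To evaluate the benefits and differences of the biofeedback study, classification analyses will be performed on the data".

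On the arms, section 3 (Methods/design) calls the study non-randomised, with assignment by order of enrolment. Comparability is to be confirmed by finding no significant difference at inclusion; the variables named are age, sex and whether the earthquake was experienced as traumatic.

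Pre-treatment data exist. Section 3.1.2 says that "measurements will be performed during the information session, at the beginning of the sessions", and the caption of Figure 1 reads "Procedure to be applied to all groups before the first session". Section 3.5.1 compares the primary outcomes RMSSD, HF and LF at the final session with the first session, by a mixed model with group and time or by ANCOVA. It makes the other measures, including electrodermal activity and neuroimaging, exploratory secondary endpoints.

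**The concern.** Neither classification identifies a treatment effect alone. The arm contrast mixes any effect with whatever already distinguished the arms at entry. The before/after contrast within one arm has no comparator, so it also absorbs habituation and repetition of the stress task. A treatment effect is a difference between arms in change, and section 3.4 never forms that contrast.

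Entry differences are a realistic risk. Data collection ran from December 2024 to June 2025, and the Limitations section accepts that season affects physiological parameters. If enrolment order placed the arms in different months, the classifier inputs themselves could be shifted. The article does not say whether arms were filled in blocks or in rotation, so this is a possibility and not a demonstrated imbalance.

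At stake is the deep-learning evidence that is meant to show benefit. A network could separate control from treated participants with no treatment effect, and the plan would read that as a significant difference. Careful data splitting does not cure this, because a true entry difference also holds in people kept out of training.

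**Working it through.** **The plan's own figure.** Section 3.5.2 gives 1980 segments per measurement: 330 min × 60 s ÷ 10 s = 1980, which reproduces. Cutting recordings into segments does not add participants, who carry the arm label. The sample size rests on a rule of thumb, so there is no power calculation to reproduce.

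**The two contrasts side by side.**
- Arm against arm: between people, with no stated reference to each person's starting level.
- Before against after: within one arm, with no comparison to another arm.
- Change compared between arms: not planned for the classifiers. For RMSSD, HF and LF, section 3.5.1 does bring in the first session.

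The gap remains whichever time points feed the arm classifier. Post-treatment recordings contain entry difference plus effect. Pre-treatment recordings pooled under the same arm label also let the network learn the entry difference.

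**Size, by illustration.** Assumptions, none given in the document: one normally distributed feature, a true entry shift of d SD between arms, and no treatment effect. The best attainable balanced accuracy is Φ(d/2):
- d = 0.5: Φ(0.25) = 0.599, or 60%
- d = 0.8: Φ(0.40) = 0.655, or 66%
- chance: Φ(0) = 50%

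**Effect of referring to baseline.** This was simulated for a single feature with zero treatment effect, an assumed pre/post correlation of 0.8, two-sided 0.05 and 3000 runs per row. The table gives the percentage of runs declared significant by a t-test between arms.

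| Entry gap (SD) | Post only, 10 per arm | Change, 10 per arm | Post only, 12 per arm |
|---|---|---|---|
| 0 | 4% | 5% | 5% |
| 0.5 | 18% | 5% | 20% |
| 0.8 | 40% | 5% | 47% |
| 1.0 | 57% | 6% | 66% |

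At 12 per arm the change comparison stays at 4–6%. These are t-tests and not networks, so they show direction and mechanism, not the accuracy that the planned networks would reach.

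**Would the comparability check catch such gaps?** It names no biosignal. Applied to one at 10–12 per arm (normal approximation, assumed two-sided 0.05), it would have 20–23% power for a 0.5 SD gap and 43–50% for a 0.8 SD gap. Gaps of this size can pass.

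**The case against.** **Pre-treatment data are used.** A reader might infer that the arm classification uses no pre-treatment data. The documents do not support that. The same sentence of section 3.4.2 plans before/after contrasts, and section 3.4 says that changes "before, during, and after the intervention will be analyzed". The text does not say which time points enter the arm classifier, and silence is not exclusion. What stands is narrower: the two contrasts are not joined.

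**This may be detail for the statistical analysis plan.** The article mentions such a plan, and it is not shown. Choice of recordings could well belong there. But the article itself fixes both contrasts and the inference to be drawn from them, so the point is more than missing detail.

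**The main estimate uses baseline.** True, and the study calls itself preliminary. This limits the point to the classification evidence. The mixed model or ANCOVA is stated for RMSSD, HF and LF only.

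**The size could be overstated.** A reader might take 0.94 SD as the largest gap that the comparability rule lets pass. That figure is the cut-off for an observed difference at 10 against 10, 2.101 × √(2/10), at a significance level that the article does not state. The cut-off is 0.79 for 10 against 20 and 0.85 for 12 against 12. An observed cut-off is not a true shift, so it should not be put into Φ(d/2). Also, with 20 people, 14 or more correct (70%) arises by chance in about 5.8% of cases. A participant-level classifier would thus often fail to distinguish 60–66% from chance. Systematic entry differences are assumed here, not shown.

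**Another defect may be larger.** Section 3.5.2 says that splitting by individual would need more participants. With windows from one person in both training and test sets, a simulation with no group or treatment difference gave 70–99% accuracy (assumed between-participant variance share 0.5–0.9), against about 50% when split by participant. That is a separate problem; solving it would leave this one.

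**Conclusion.** The point holds in a limited form. The arm and before/after classifications are planned separately, are meant to show a significant difference and benefit, and are never combined into a between-arm comparison of change. With non-randomised arms and no biosignal named in the comparability check, an entry difference and a treatment effect cannot be told apart in the arm result.

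The size is illustrative: 60% or 66% best balanced accuracy for one feature truly shifted by 0.5 or 0.8 SD, with no treatment effect. The shifts, normality and the pre/post correlation are assumptions. The documents establish neither that an imbalance occurred nor that pre-treatment data are left out, and the primary RMSSD, HF and LF analysis is not affected by this point. The change should be made, since this evidence is intended to support benefit, but it concerns exploratory analyses.

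**What to change.** - **Numerical features (section 3.4.3):** classify arms on each participant's change from the pre-treatment value, matched by stage.
- **Signal and image networks (sections 3.4.1 and 3.4.2):** run the same arm classifier, with the same participant-level split, on pre-treatment recordings as a negative control. Match the stage: calm against calm, and stress against stress only where a pre-treatment or first-session stress recording exists. A calm recording is not a like-for-like reference for stress data. Section 3.1.2 places stress tasks in the sessions and at four weeks, and gives sound before and during stress, so first-session recordings may already include stimulation. State this wherever they serve as the reference.
- **Inference:** attribute to treatment only the excess of post-treatment over pre-treatment accuracy, with an interval computed at participant level. Where no matched reference or participant-level split is available, report the arm classification as descriptive and drop the claim that it shows a significant difference.

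The cost is a rerun on recordings already planned, with no new data. The price is less favourable accuracies and a difference of two noisy accuracies that will be imprecise at this sample size. The participant-level split is also one that section 3.5.2 regards as needing more participants.

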Study type	Allocation: non-randomized Intervention model: parallel assignment Primary purpose: treatment
Date of first enrollment	December, 2024.
Target sample size	36
Recruitment status	Recruiting.
Primary outcome(s)	Method of measurement: Biopotentials (ECG, PCG, EDA, fNIRS, respiratory rhythm) Timepoint: pre-treatment, post-treatment, and follow-up.
Key secondary outcomes	Changes in neuroimaging measures Timepoint: pre-treatment, post-treatment, and follow-up. Changes in biopotential measures Timepoint: pre-treatment, post-treatment, and follow-up.
Ethics Review	This project received ethical approval from Harran University with the decision of the clinical research ethics committee on 03 July 2024.
Completion Date	October, 2025

The SPIRIT reporting guidelines recommend these items to be included in trial protocols to provide a brief, structured overview of a trial.

Our study is a non-randomized, parallel-group cohort study. Patients were assigned to a group in the chronological order of enrollment in the study. Therefore, consecutive sampling was used for allocation concealment. The inclusion and exclusion criteria will be applied uniformly to all patients, regardless of group, without exception. At inclusion, baseline characteristics will be compared between groups, including age, sex, and whether participants experienced the earthquake as a traumatic event. The comparability of the groups at inclusion will be verified by ensuring that there are no significant differences between groups.

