From the study of Gerdes et al., public treatment centers called “Cereset” were opened on the American and European continents. Similar to physiotherapy centers, these centers offer relaxation methods over 10 sessions within 4 weeks by acting on the patient’s parasympathetic system using EEG signals (Tegeler et al., 2023). For post-traumatic therapy sessions, 10 sessions of 30 min each are considered sufficient (Desbiendras, 2024). In this context, the participants will have 10 sessions over approximately 4 weeks (S1-S10). According to the literature, 10 sessions are sufficient for effective intervention and adequate observation. Participants will receive the first two sessions on consecutive days. Then, participants will have two sessions in a half-day period with a 1-h break between sessions. Participants will receive the third session within the first 5 days. Participants will complete the rest of the 10 sessions, with a maximum of 5 days between sessions. The sessions will occur between 1:00 and 5:00 p.m. ±30 min, as the participants may better remember emotionally stimulating information in the afternoon (Maheu et al., 2005). In addition, according to Figures 1–3, the transitions between stages will be direct and immediate without a break. In addition, the date of menstrual onset will be recorded to account for the menstrual periods of female participants.

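### Before-versus-after classification within a group is to show significance and benefit, but it cannot separate treatment from time changes shared by all arms

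*Protocol article*

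**What the plan says.** Section 3.4 (Data analysis) gives the classifiers their purpose: "To evaluate the benefits and differences of the biofeedback study, classification analyses will be performed on the data". Two contrasts follow. Section 3.4.1 classifies control against treatment, and also "between the results of the same group before and after treatment", on recordings made during mental stress. Section 3.4.2 repeats both contrasts for ECG, electrodermal and fNIRS data. It describes the second as characterising differences between arms "as well as differences before and after treatment within groups and to show that the difference is significant".

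Section 3.1.2 (Study design) sets ten sessions over about four weeks and a follow-up about four weeks later. On the stressor it says: "Different mental stress tasks will be induced in all sessions and 4 weeks after the sessions". The stated safeguard against practice is that "the mental operations should be randomized in order to create stress without allowing learning to occur". There is a silent control arm, and "The intervention and control groups will be exposed to the same mental stress". Table 1 records "Allocation: non-randomized", and Section 3 adds that groups were filled in chronological order of enrolment. Section 5 (Limitations) accepts that season affects the physiological signals and that recordings may not all fall in one season.

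The primary pilot outcomes (RMSSD, HF and LF) are handled separately in Section 3.5.1. They are compared between first and final session by a linear mixed model with group and time, or by ANCOVA.

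**The concern.** A before/after difference inside one group answers whether recordings changed over the intervention period. It does not answer whether the sound changed them. Participants in every arm meet the stress procedure at ten sessions, and calendar time passes for all of them. Any resulting change that participants share separates early from late recordings, with or without sound. A classifier trained on that contrast is rewarded for finding it.

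The document goes beyond describing this contrast. It is one of the two by which a significant difference is to be shown, and classification is the stated route to evaluating benefit. A null intervention could then be reported as beneficial because before and after are separable in a treated arm. The silent arm supplies what is needed to remove the shared change, but no section sets a treated arm's before/after result against the control arm's.

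**Working it through.** **The plan's own figure.** The only number attached to the classifiers is the count of 10-second windows in Section 3.5.2: 330 min × 60 / 10 = 1,980 for each measurement. It reproduces. No alpha, effect size or expected accuracy is stated, so nothing else can be reproduced.

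**Inputs.**
- From the document: 10 per group (Section 3.1.2), or 36 / 3 = 12 per group (Table 1 target, three arms).
- Assumed: a time shift identical in all arms, zero treatment effect and two-sided alpha 0.05. The size of the shift is not in the document, so a range is used.

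**Step 1: accuracy from one feature.** Take two normal distributions with equal variance, shifted by *d* SDs of the feature. The best achievable accuracy is Φ(d/2).
- d = 0.3: Φ(0.15) = 0.56
- d = 0.5: Φ(0.25) = 0.60
- d = 0.8: Φ(0.40) = 0.66

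Chance is 0.50. The control arm is expected to give the same values, because the shift is common.

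**Step 2: false-positive rate of a within-group test.** The plan names no test for the classification, so a paired t-test on before/after change stands in. Here the shift *h* is in SDs of the change, a different scale from *d*. The rejection probability comes from the noncentral t with n − 1 degrees of freedom and noncentrality h√n. The comparator is a two-sample t-test of treated change against control change (20,000 simulations).

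| h | Within one group, n = 10 | Within one group, n = 12 | Treated vs control change, n = 10 | Treated vs control change, n = 12 |
|---|---|---|---|---|
| 0 | 0.05 | 0.05 | 0.047 | 0.049 |
| 0.3 | 0.136 | 0.158 | 0.052 | 0.051 |
| 0.5 | 0.293 | 0.353 | 0.050 | 0.052 |
| 0.8 | 0.616 | 0.714 | 0.050 | 0.050 |
| 1.0 | 0.803 | 0.883 | 0.050 | 0.048 |

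There are two treated arms, so the chance that at least one is significant is 1 − (1 − p)². For h = 0.3 and n = 10 this is 1 − 0.864² = 0.254. For h = 0.8 and n = 12 it is 1 − 0.286² = 0.918.

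**Step 3: what survives a split by participant.** An illustrative 5-nearest-neighbour classifier was run with 12 people, 60 windows per session, 10 features and 200 simulations, again with no treatment effect.
- Random person-by-session differences (SD 0.5), no shared shift: accuracy 72% when windows are split at random, 50% when split by person.
- Shared shift in one of the ten features, no random session differences, split by person: 52% for a shift of 0.5 and 55% for 0.8.

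In this run the shift is in SDs of window noise, person-to-person variation is added, and nine features carry no signal. The accuracies therefore fall below those in Step 1. A shared shift survives a split by participant; random session-to-session differences do not.

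**The case against.** The case against has real force on several points.

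*The wording is not limited to treated arms.* Section 3.4.2 says within groups, in the plural, beside a control-versus-treatment classification. A reader might infer that the silent arm is left out of the before/after analysis. The document does not say so, and the arm may well be included. But running the same classifier in each arm does not cure the inference unless the results are compared. The planned control-versus-treatment classification is a different contrast from a comparison of changes.

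*Such detail usually sits in an analysis plan.* That is true of how accuracies are weighed. The point here rests on the role that the article itself gives to the within-group contrast.

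*It is not the main inference.* This stands. A reader might infer that the primary analysis is compromised, but Section 3.5.1 is separate and the study is presented as preliminary. That section covers only RMSSD, HF and LF, so it does not protect the ECG, electrodermal and fNIRS classifications.

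*Habituation is not documented.* Correct. A reader might take it as established that ten repeats change the response. The document gives no such figure, and it plans varied tasks and randomised operations. That is a reasonable intention against item learning and need not be withdrawn. It does not address familiarity with the procedure or season, and the conclusion needs only some shared change.

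*Sensor placement.* It is tempting to add day-to-day differences in placement as a further cause. Where these are random, they belong to the question of how windows are split (Section 3.5.2), as Step 3 shows, and do not support this point.

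*Treated-minus-control accuracy.* This looks like the natural remedy, but accuracy has no sign. A control shift of +0.5 SD and a treated shift of −0.5 SD each give 60%. The difference is 0, although the changes differ by 1 SD.

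**Conclusion.** The concern holds in a limited form. Sections 3.4 to 3.4.2 assign before/after classification within groups a part in showing significance and benefit, and that contrast cannot tell treatment from a time change shared by all arms. With no treatment effect, an assumed shared shift of 0.3 to 0.8 SD allows 56% to 66% single-feature accuracy. On the scale of SDs of change, the same range makes a before/after test in one group of 10 to 12 significant in 14% to 71% of trials, against about 5% for treated versus control change. These sizes depend entirely on the assumed shift; at zero shift the test keeps its 5%. The direction of the problem needs only that some shared change exists, and Section 5 itself accepts season as one possible source.

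The 5% figure also assumes that the shift is equal across arms. With non-randomised, chronological allocation that is not assured, so a between-arm comparison of change is better but not secure.

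**What to change.** In Sections 3.4.1 and 3.4.2:

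- Label before/after classification within groups as descriptive in every arm, control included. State that it is not used alone as evidence of significance or benefit.
- Base any claim of benefit on a comparison of change between treated and control participants that keeps direction. Examples are the group-by-time contrast on the features listed in Section 3.4.3, or classification of each participant's before-to-after change by arm.
- Make the participant the unit for splitting and resampling.
- Report the control arm's change as the estimate of shared time effects.
- State that allocation was non-randomised and chronological, so even this contrast needs cautious reading.

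Section 3 reports data collection as completed by 30 June 2025, so the cost is analysis wording and further runs on data already in hand. The downside is that within-group accuracies can no longer be presented as benefit. With 10 to 12 participants per arm, the interval around the treated-versus-control comparison will also be wide.
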